#### Secondary outcome measures

The secondary outcomes as listed below are;

The craving level, as indexed by self-report using the Desire for Drugs Questionnaire (DDQ) and a visual analogue scale (VAS). The DDQ is validated instrument [35] which measures an instant desire, triggered by internal or external cures (instant craving). Franken and colleagues [35] identified three factors as underlying dimensions, namely ‘desire and intention’ (seven items), ‘negative reinforcement’ (four items), and ‘control’ (two items) with a scale from 1 (totally disagree) to 7 (totally agree). The total score exists of 14 items with a sum score between 14 and 98 [35]. In addition to that patients were asked to rate craving for GHB by means of a visual analogue scale (VAS) on a Vertical line from no craving at all (at the bottom) with a score of 0, to extremely strong craving (at the Top) with a score of 100. The result is a score on a continuous scale ranging from 0 to 100.

A change in psychiatric symptoms will be measured by means of the Mini International Neuropsychiatric Interview-plus (MINI-plus) and Depression Anxiety Stress scale (DASS). A trained therapist or physician will apply the MINI-plus. It is a structured interview to assess the main Axis I psychiatric disorders based upon the DSM–IV and ICD-10 criteria. It is used to determine current and lifetime psychiatric disorders [36]. The MINI is shown to have good psychometric properties and is reliable for the detection and classification of psychiatric comorbidity [37]. The DASS self-report will be used to measure psychiatric symptom levels and the related negative emotional states along the 3 axes of depression, anxiety and stress. It is a 21-item self-report instrument. Participants are asked to use a 4-point severity scales to rate the extent to which they have experienced each state over the past week. Scores for Depression, Anxiety and Stress are calculated by summing the scores for the relevant items. For each scale threshold values are proposed and are interpreted in 5 severity intensities: normal, mild, moderate, severe and extremely severe. Thresholds as (for Depression ≥ 21; for Anxiety ≥15; for Stress ≥ 26) indicate a severe or extremely severe distress state [38,39].

The EuroQol-5D (EQ-5D) will be used to measure changes in patients’ health-related quality of life. For the overall quantification of health status as a single index we will use the standard EQ-5D classification system developed by the EuroQol Group [40]. The EQ-5D is a widely used multi-attribute system available to determine health state preferences (utilities). It is a simple self-report instrument which assesses 5 domains of general health and functioning: mobility, self-care, usual activities, pain/discomfort and anxiety/depression. This is along a 3-point scale (1 = no problems, 2 = some problems and 3 = extreme problems). Based on the descriptive classification of the EQ-5D system a preference index (utility) can be estimated that expresses the overall preference of the classified health status [41] [the Netherlands algorithm will be used to calculate the index]. This EQ-5D index measures objective quality of life and is a societal-based numerical quantification of the patients’ health status in a scale from-.594 to 1 (perfect health), 0 is (as bad as being dead). In addition, participants will be asked to rate the overall health related quality of life, by means of a visual analogue scale (EQ-5D VAS). The VAS is a 100-mm vertical line from worst (0) to optimal of health (100). The EQ-5D VAS represents the subjective quality of life.

Safety of baclofen will be assessed by the number and intensity of reported side effects, using weekly report of adverse effects on a checklist and standardized medical assessments. The side-effects checklist is based on published side effects of baclofen in the treatment of Multiple Sclerosis [42]. Side-effects are partly self-monitored (21 items) and partly observed (8 items) by a doctor or nurse practitioner. Every item is scored on a five-point Likert scale: never (0), seldom (1), sometimes (2), frequently (3) or always (4). Examples of items are vomiting, nausea and diarrhea. The checklist also contains 5 parameters measured by a doctor or nurse practitioner. Examples of parameters are body temperature and heart rate frequency.

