Safety of baclofen, as assessed by the number and intensity of reported side effects, will be analyzed in the following categories: acceptable or unacceptable adverse effect, clinically significant deterioration, and relocation. In all analyses socio-demographic characteristics such as age and gender will be considered as co-variates in the analysis. Two-sided p-value of > .05 is considered statistically significant. The statistical software package SPSS will be used for all the computations.

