### Implications for practice

If our study confirms the potential of baclofen to reduce relapse and craving without serious adverse events in GHB-dependent patients, this warrants large scale randomized controlled trials in order to draw more firm conclusions. If baclofen showed to have beneficial effects on psychiatric symptoms in these patients, baclofen might be specific interest for the treatment of those GHB dependent patients with co-morbid high levels of anxiety and depression.

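### The safety outcome promises the intensity of side effects, but the only symptom score described records how often they occur

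*Protocol article*

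**What the plan says.** Under Secondary outcome measures, the protocol article states: "Safety of baclofen will be assessed by the number and intensity of reported side effects, using weekly report of adverse effects on a checklist". The same sentence adds standardised medical assessments as a second source. The checklist is then described: "Side-effects are partly self-monitored (21 items) and partly observed (8 items) by a doctor or nurse practitioner", and "Every item is scored on a five-point Likert scale: never (0), seldom (1), sometimes (2), frequently (3) or always (4". Separately, "The checklist also contains 5 parameters measured by a doctor or nurse practitioner", with body temperature and heart rate as examples.

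Under Statistical analyses the same definition returns: "Safety of baclofen, as assessed by the number and intensity of reported side effects, will be analyzed in the following categories". The categories are "acceptable or unacceptable adverse effect, clinically significant deterioration, and relocation".

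Under Implications for practice, a large randomised trial is said to be warranted if baclofen can "reduce relapse and craving without serious adverse events".

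**The concern.** The outcome is named for one attribute and scored on another. Intensity is how bad a symptom is; a scale from never to always records how often it is present. If the 0 to 4 score is what gets reported as intensity, the result will carry a meaning that it does not have.

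The fault lies in data capture. Two patients can both tick seldom for vomiting, one after a trivial episode and one after a severe one, and no later analysis of the scores can tell them apart. A statistical analysis plan could not repair this if severity was never recorded at the visit.

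At stake is a named secondary outcome and one of the stated expectations under Aims and hypotheses, namely that side effects will be minimal. Judging an adverse effect acceptable or unacceptable also calls for some view of severity.

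**Working it through.** The plan gives no figure to reproduce here. The check sets the outcome definition against the measuring scale, and then looks for any other described source of intensity.

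1. **Attributes promised.** Number and intensity (Secondary outcome measures; repeated in Statistical analyses).

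2. **Items scored.** 21 self-monitored + 8 observed = 29 items, all on the same 0 to 4 scale. The 5 measured parameters are listed apart from these.

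3. **What the anchors measure.** Never = 0, seldom = 1, sometimes = 2, frequently = 3, always = 4. Each is a frequency word and none refers to severity.
   - *Number* can be derived by counting the items scored 1 or more, which gives 0 to 29 per completed checklist.
   - *Intensity* cannot be derived, because the score for an item depends on occurrence only.

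4. **What this does within one item.** Vomiting is one of the three example items that the article names.
   - One severe episode in the reporting period: seldom = 1, at most sometimes = 2.
   - A mild complaint every day: always = 4, at least frequently = 3.
   - The highest plausible score for the severe single episode (2) is below the lowest plausible score for the mild daily complaint (3). The order is the same under either reading. Matching these cases to anchors is an assumption, because the article does not say how many occurrences each word covers.

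5. **Is intensity just a loose word for frequency here?** The same section describes the DASS with a 4-point severity rating and five named bands from normal up to extremely severe, and there intensity refers to severity. The safety checklist has no comparable grading.

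6. **Is intensity described anywhere else?**
   - Medical assessments: named, but not said to grade the severity of symptoms.
   - Measured parameters: the examples are vital signs, not grades of the 29 items.
   - Analysis categories: no rule is given that leads from the 0 to 4 scores, or from the medical assessments, to a category.

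7. **Is there a visit at which severity could be recorded?** In Table 2 the side-effect checklist is marked in weeks 0, 1, 2, 3, 4, 7, 10 and 12. A medical consult is marked in each of those eight weeks.

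**The case against.** The strongest reply is that the checklist is not the whole safety assessment. The protocol article also names medical assessments, measured parameters, regular consults and blood tests, and the physician adds a summary of the medical records to the patient file. The analysis is by category, so a clinician could place a single severe event among the unacceptable effects whatever its checklist score. A journal article may also leave severity grading and the handling of serious events to the full protocol.

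Much of this stands, and it rules out several stronger conclusions that a reader might draw:

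- *That severe events would go undetected.* The other sources may well reveal them.
- *That patients would be ranked in reverse order of harm.* The article nowhere sums the 0 to 4 scores or ranks patients by them.
- *That the ratio of two scores measures the size of the error.* The anchors are ordinal and undefined, so only the order in step 4 can be used.
- *That the statement on serious adverse events, or the decision on a further trial, rests on this score.* The article does not say that serious events are taken from the checklist, and it makes further trials depend on relapse and craving as well.

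The reply does not remove the mismatch itself. The article states the scale, applies it to every item, and names intensity as part of what is assessed and analysed. That is a stated measure that does not fit its stated outcome, which is different from detail left out for brevity.

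**Conclusion.** The point holds in a limited form. As described, the checklist yields the number and frequency of side effects on 29 items and cannot supply their intensity. No other described source is said to grade symptom severity, and the path from scores to safety categories is not stated. This should be corrected before safety results are reported under the present label.

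The effect is confined to a secondary outcome in a study that the article itself calls explorative. The primary outcome, the sample size and the error rates do not change. How far any safety result would be distorted cannot be quantified from the document. The example in step 4 shows direction only and rests on the ordinary meaning of the anchor words. The conclusion also assumes that the article describes the checklist as it is used; if the full protocol already records a severity grade, only the wording and the missing link to the categories need correction.

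**What to change.** 1. Keep the 0 to 4 score and report it as frequency.
2. For each item scored 1 or more, have the clinician at the existing consult record a severity grade (mild, moderate, severe) and whether the event was serious.
3. Base the intensity result and the safety categories on those two fields together with the medical assessments, and state the rule that assigns a category.
4. Align the wording under Secondary outcome measures and Statistical analyses.

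If the form can no longer change, rename the outcome number and frequency of side effects, and draw no conclusion on intensity from the checklist.

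The cost is two extra fields per reported item, slightly longer visits and a wording change in two sections. No extra visit is needed, since Table 2 already places a consult in every week that has a checklist.

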#### Additional measures

Addiction physicians will be asked to monitor withdrawal symptoms when tapering baclofen, using standard questions. These include a short check of the most reported withdrawal symptoms in the literature [43,44].

We will monitor the use of other substances over the last thirty days (number of days and quantity) using section 1 of the Measurement of Addicts for Triage and Evaluation (MATE) before and after detoxification and at follow up (3 months). The MATE is a Dutch instrument designed as an aid in the diagnosis of clinically relevant patient characteristics in substance use disorders according to the DSM-IV axes [45].

At 6 month period we will also report on the needed period of treatment with baclofen to maintain abstinence by monitoring relapse (Timeline Follow back) and craving assessment (DDQ, VAS) within the intervention group between those who used baclofen for 3 month only and those who choose to continue the treatment further.

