**Table 2 Tab2:** **Time measurements**

**Week**	**0**	**1**	**2**	**3**	**4**	**5**	**6**	**7**	**8**	**9**	**10**	**11**	**12**	**13**	**14**	**15**	**24**
Measurement	**T0**-baseline	**T1**											**T2**				**T3**
Mate section	xx												xx				x
EQ–5D	xx												xx				x
DASS	xx												xx				x
Mini-plus	xx												xx				x
Blood	xx						x						x				
Urine	xx						x						xx				x
Medical consult	2x	2x	2x	x	x			x			x		x	x	x		
Baclofen (mg)	0	15–30	45– 60											30–45	30–15	15–0	0
Baclofen Side effect	x	2x	2x	x	x			x			x		x				
VAS	xx	x	x	x	x			x			x		xx				x
DDQ	xx	x	x	x	x			x			x		xx				x
Baclofen withdrawal checklist														x	x	x	
Timeline follow back													xx				x

xx = baclofen group and control group TAU only.

x = baclofen group.

T0 = end of GHB detoxification.

T1 = start baclofen treatment.

T2 = follow-up TAU only and end of baclofen therapy.

T3 = follow-up baclofen group.

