## Discussion

This study protocol presents the design of an open label clinical trial evaluating the efficacy of baclofen to prevent relapse, reduce craving and anxiety, and to assess the safety profile of baclofen in GHB dependent patients. To date, there are no reports on the potential of baclofen to prevent relapse in GHB dependent patients. We expect that baclofen will increase abstinence rates, reduce craving and will be well tolerated. In addition, baclofen may improve psychiatric symptoms such as anxiety and depression, as suggested in several clinical trials in alcohol-dependent individuals [29,30,46].

Several risks of baclofen use are taken into account in the current study. In patients with neuropsychiatric disorders, such as schizophrenia, severe depression, mania, Parkinson’s disease and cerebrovascular diseases, exacerbations of these conditions may occur, when the dose of baclofen is rapidly increased. It may lower the threshold for seizures in epileptic patients [42]. To limit these risks in the current trial, baclofen will be uploaded gradually, over a period of minimally 10 days. Moreover, patients previously diagnosed with any of the mentioned diseases will be excluded from the study.

Abrupt discontinuation of baclofen, when used for several months, can be associated with a withdrawal syndrome which resembles benzodiazepine and alcohol withdrawal. Several symptoms are reported such as hallucinations, fever, confusion, delirium, agitation, insomnia, and muscle stiffness and spasms [47]. Therefore, patients will be advised to taper down slowly when discontinuation is needed.

Intoxication with baclofen has been reported in doses above 100 mg [48]. This risk increases if patients combine baclofen with GHB. Intoxication is not expected when baclofen is administered at a low dose (<30 mg per gift), as applied in the current study. Patients will however, be informed repeatedly of this potential risk and the treatment will be discontinued immediately in case of relapse.

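### The baclofen withdrawal checklist has no full-dose score and no TAU comparator, so symptoms in the taper cannot be cleanly separated from background symptoms

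*Protocol article*

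**What the plan says.** Under Additional measures the protocol article states: "Addiction physicians will be asked to monitor withdrawal symptoms when tapering baclofen, using standard questions". On content it adds: "These include a short check of the most reported withdrawal symptoms in the literature". The questions themselves, their scoring and any rule for attributing a symptom to withdrawal are not given.

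In Table 2 the row "Baclofen withdrawal checklist" has a single x at weeks 13, 14 and 15 and nowhere else. The legend reads "x = baclofen group", so TAU-only patients do not receive it. The row "Baclofen Side effect" is marked at weeks 0, 1, 2, 3, 4, 7, 10 and 12. The DASS and MINI-plus are marked at weeks 0, 12 and 24. A medical consult is marked at week 12 and again at weeks 13 and 14.

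The Discussion says that stopping baclofen abruptly after several months "can be associated with a withdrawal syndrome which resembles benzodiazepine and alcohol withdrawal". The symptoms it lists range from insomnia, agitation, confusion and muscle stiffness to delirium, hallucinations and fever. The Background reports more anxiety and depression after patients stop GHB.

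**The concern.** A symptom seen in week 13, 14 or 15 may have started with the taper. It may also have been present at full dose, been left over from GHB dependence, or followed a lapse. Telling these apart needs either the patient's own score on the same questions before the taper or a concurrent group answering the same questions. The schedule provides neither.

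The instruments also change over where the dose starts to fall: the side-effect checklist ends at week 12 and the withdrawal checklist begins at week 13. In Table 2 no symptom instrument is completed both at full dose and during the taper. What is at stake is whether the taper data can be read as change. No efficacy result depends on them.

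**Working it through.** **Schedule in Table 2**

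| Measure | Up to week 12 | Weeks 13-15 | Week 24 |
|---|---|---|---|
| Withdrawal checklist | none | 13, 14, 15 | none |
| Side-effect checklist | 0, 1, 2, 3, 4, 7, 10, 12 | none | none |
| DASS, MINI-plus | 0, 12 | none | yes |
| Urine | 0, 6, 12 | none | yes |
| Medical consult | 0, 1, 2, 3, 4, 7, 10, 12 | 13, 14 | none |

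Only the consult itself crosses from week 12 into the taper, and no symptom instrument goes with it on both sides.

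**Can the week-12 measures stand in?** Only partly. The side-effect checklist is a separate instrument: "Side-effects are partly self-monitored (21 items) and partly observed (8 items) by a doctor or nurse practitioner". It is drawn from baclofen side effects in multiple sclerosis and scored by frequency from 0 to 4. The withdrawal questions come from the withdrawal literature. The article does not show which items overlap. The DASS covers depression, anxiety and stress only.

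**Size.** The plan gives no figure on this point to reproduce, and no background rate. The two illustrations below use assumed values.

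*Illustration 1: background plus true onset.* Let b be the share of patients with a background symptom, and w the share of the remaining patients in whom one truly starts during the taper. The rate seen in the taper is b + (1 - b)w, and the background share of positives is b / [b + (1 - b)w].

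| b | w = 10%: rate seen | background share | w = 20%: rate seen | background share |
|---|---|---|---|---|
| 0% | 10% | 0% | 20% | 0% |
| 10% | 19% | 53% | 28% | 36% |
| 30% | 37% | 81% | 44% | 68% |
| 50% | 55% | 91% | 60% | 83% |

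For example, with b = 30% and w = 10%: 0.30 + 0.70 × 0.10 = 0.37, and 0.30 / 0.37 = 81%. Without a pre-taper score, b and w cannot be told apart in the data.

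*Illustration 2: which summary repairs this.* Assume no true withdrawal, and a share p of patients with a symptom in any week, independently from week to week.

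- Any symptom at any of three taper checks: 1 - (1 - p)³.
- Absent at week 12 but present at any taper check: (1 - p)[1 - (1 - p)³].
- In one given taper week, new against week 12: (1 - p)p. Resolved against week 12: p(1 - p). Net: zero.

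| p | Any of three checks | New at any of three | New in one week | Resolved in one week | Net |
|---|---|---|---|---|---|
| 10% | 27% | 24% | 9% | 9% | 0 |
| 20% | 49% | 39% | 16% | 16% | 0 |
| 30% | 66% | 46% | 21% | 21% | 0 |
| 40% | 78% | 47% | 24% | 24% | 0 |

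If symptoms persist fully instead, a taper-only tally shows p itself, and new, resolved and net are all zero. A pre-taper score therefore helps only if improvement is counted as well as worsening. A count of new symptoms alone would still show 24-47% in the independent case with no withdrawal at all.

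**The case against.** A reader might infer that every symptom recorded in weeks 13-15 will be counted as baclofen withdrawal. The article does not say so. It states no counting or attribution rule and no analysis of this checklist; the safety analysis it describes concerns side effects. A reader might also infer that the study sets out to report how safely baclofen can be stopped. That is not among its stated aims or outcomes. The checklist is an additional measure and may serve mainly as bedside monitoring, which needs no baseline.

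Other points on that side also carry weight:

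- The questions are not reproduced and may already ask about new or worse symptoms.
- The physician who sees the patient at week 12 and in the taper can use judgement.
- The week-12 DASS, MINI-plus and side-effect checklist (which includes body temperature) describe the patient before the taper.
- The Timeline Follow-back at week 24 can recover GHB lapses by recall.
- Some listed signs, such as delirium and hallucinations, are unlikely as routine background.
- The secondary-outcomes text calls side-effect reporting weekly. If that ran into the taper, one instrument would span it, but Table 2 ends it at week 12.
- Patients who stop early or continue baclofen would not taper in weeks 13-15.

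These points limit the concern but do not remove it. Judgement and partial context are not a score on the same questions, and an attribution rule would be hard to apply reliably without one.

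**Conclusion.** The point holds in a limited form. As scheduled, the withdrawal checklist has no same-instrument score at full dose and no TAU comparator, so it describes symptom prevalence in the taper and cannot cleanly separate taper-related from background symptoms.

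The size of any misattribution is unknown. The background rates of 10-50%, the onset rates of 10% and 20%, and the any-of-three-checks tally are assumptions made for illustration; none stands in the documents. The conclusion rests on Table 2 as printed and on some of the listed symptoms being non-specific. The primary outcome, the sample size and the planned tests are unaffected, and the study calls itself explorative. The change is worth making because it is cheap and a pre-taper score cannot be collected once the taper has begun.

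**What to change.** In Table 2, add the same withdrawal checklist at the existing week-12 medical consult. For patients who continue baclofen, place it at the last visit before their own taper and repeat it during that taper.

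Add a sentence on reporting: for each taper week, give the paired within-patient change from the pre-taper score, showing both new or worse and resolved or improved symptoms, and the net change. Describe the result as uncontrolled change during the taper, not as proven baclofen withdrawal. Net change is centred on zero only if background symptoms are stable over those weeks, and without a concurrent comparator the contrast cannot show that the taper caused the change.

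The cost is one table mark, a sentence, and a few extra minutes per baclofen patient. No dose, taper or stopping rule is touched. Separately, the Baclofen intervention text gives a taper of two weeks while Tables 1 and 2 show reductions over weeks 13-15; these should be reconciled so that the pre-taper visit is unambiguous.
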